### Data collection and study procedures

After obtaining written informed consent, the following clinical characteristics will be recorded for each patient: demographics, socioeconomic parameters, complete medical history and medication, prior diagnostic and therapeutic interventions. A self-reported measurement of patients’ physical activity will be provided using the International Physical Activity Questionnaire (IPAQ), which will be completed by each patient before discharge. IPAQ is a validated questionnaire utilized to objectively measure and stratify physical activity by dividing populations into three levels: low, moderate and high physical activity [13]. Obesity will be diagnosed by categorization of body mass index (BMI; Kg/m2) measured before echocardiographic study. Recorded socioeconomic parameters will include education, marital status, employment, income, migration background and ethnicity. Moreover, the 36-item short form (SF-36) standardized questionnaire will be administered to obtain a self-reported measure of their health-related perception of quality of life before the AMI. In addition, patient laboratory data will be recorded on admission and during hospitalization. These include total blood count, standard biochemistry parameters, coagulation tests, thyroid hormone and thyroid-stimulating hormone levels, HbA1c, NTproBNP and HsTnT levels on admission, peak values of HsTnT, and NTproBNP. Moreover, levels of LP(a), apolipoproteins B and A1 (ApoB and ApoA1) interleukin-6 (IL-6) and soluble urokinase plasminogen activator receptor (suPAR) on admission will be assessed. Additionally, coronary angiographic images of every patient will be evaluated by two experienced independent interventional cardiologists blinded as to the demographic and clinical patient characteristics. Angiographic parameters such as lesion characteristics, coronary dominance and the SYNTAX score will be calculated.

A complete and comprehensive transthoracic echocardiographic assessment (TTE) will be performed within 24 hours from admission. All TTE studies will be conducted by certified sonographers/cardiologists using high-end scanners (e.g. Vivid E95, GE Healthcare, Chicago, IL, USA). All analyses will be separately performed by two dedicated expert cardiologists, blinded to the clinical data of all participants. All cardiac chamber sizing quantification, two-dimensional (2-D) and Doppler measurements will be performed in accordance with current recommendations [14, 15]. Simpson’s biplane method will be employed for the calculation of left ventricular ejection fraction (LVEF) for the left ventricle (LV) and abnormal values of conventional LV diastolic parameters will be determined based on recently published criteria [15]. LV diastolic function parameters include mitral inflow and annular velocities and the derived trans-mitral to averaged septal and lateral annular early diastolic velocity ratio (E/e’). All right ventricular (RV) systolic function parameters including tricuspid annular plane systolic excursion (TAPSE), fractional area change (FAC), systolic movement of the RV lateral wall using tissue Doppler imaging (S’), pulmonary artery systolic pressure (PASP) will be evaluated as per current guidelines [16].

Two-dimensional (2D) speckle tracking echocardiography will be employed to calculate strain measurements for the LV, left atrium (LA), and RV. Global longitudinal strain (GLS) will be derived from the calculation of the average of the peak systolic longitudinal strain of all segments for each chamber. To estimate myocardial work indices, LV GLS and peak systolic LV pressure measurements will be integrated to the aforementioned module [17]. Four different indices of myocardial work will be calculated including (i) LV global work index (LVGWI, mmHg %), representing the total work within the LV pressure-strain loops, (ii) LV global constructive work (LVGCW, mmHg %), defined as the work performed during myocardial shortening in systole and the work during myocardial lengthening in isovolumic relaxation, (iii) LV global wasted work (LVGWW, mmHg %), representing the work contributing to the lengthening of the cardiac myocytes during systole and the shortening during isovolumic relaxation, and (iv) LV global work efficiency (LVGWE, %), defining the percentage of effectively spend work by the LV myocytes and obtained by the following formula: (LVGCW/[LVGCW + LVGWW]) × 100%.

The primary outcome of the study is to compare clinical, laboratory and imaging parameters among SMuRF-less patients and patients with SMuRFs, thereby exploring clinical, laboratory, echocardiographic and angiographic biomarkers potentially associated with SMuRF-less status in AMI. Subsequently, we aim to assess these parameters as potential independent predictors of SMuRF-less AMIs (logistic regression analysis). Secondary goals include a comparison of short- and long-term mortality and major adverse cardiovascular events (MACE), as well as of the complexity and severity of CAD, between AMI patients with and without history of SMuRFs (Fig. 1). Short-term outcomes include all-cause death and MACE during hospitalization and/or 30 days after hospital admission. Patients will also be followed-up for a median period of 24 months after enrollment to evaluate long-term prognosis. All deaths will be ascertained by searching in the Greek web-based national health insurance system. Apart from death, MACE will be documented by independent physicians either through hospital reports or via in-person or telephonic interviews. The first patient was enrolled in April 2022 and completion of enrolment is expected until August 2023.

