**Methods:**

The ‘‘Beyond-SMuRFs Study’’ is a prospective, non-interventional cohort trial designed to enroll patients with AMI and no previous coronary intervention history, who undergo coronary angiography in two academic hospitals in Thessaloniki, Greece. The rationale of the study is to investigate potential relations between SMuRF-less AMIs and the clinical, laboratory and imaging profile of patients, by comparing parameters between patients with and without SMuRFs. Complete demographic and comprehensive clinical data will be recorded, Venous blood samples will be collected before coronary angiography and the following parameters will be measured: total blood count, standard biochemistry parameters, coagulation tests, hormone levels, glycosylated hemoglobin, N- terminal pro-B-type natriuretic peptide and high-sensitivity troponin T levels- as well as serum levels of novel atherosclerosis indicators and pro-inflammatory biomarkers. Furthermore, all participants will undergo a complete and comprehensive transthoracic echocardiographic assessment according to a pre-specified protocol within 24 h from admission. Among others, 2D-speckle-tracking echocardiographic analysis of cardiac chambers and non-invasive calculation of myocardial work indices for the left ventricle will be performed. Moreover, all patients will be assessed for angiographic parameters and the complexity of coronary artery disease using the SYNTAX score. Multivariable linear and logistic regression models will be used to phenotypically characterize SMuRF-less patients and investigate independent clinical, laboratory, echocardiographic and angiographic biomarkers-predictors of SMuRF-less status in AMI.The first patient was enrolled in March 2022 and completion of enrollment is expected until December 2023.

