Patients will be divided into two groups based on their medical history: (i) Group A: SMuRF-less patients, (ii) Group B: Patients with SMuRFs, defined as those who fulfilled at least one of the following criteria: (i) known history of hypertension and/or antihypertensive treatment prior to AMI, (ii) self-reported use of tobacco products on a systematic basis for up to 12 months before AMI, (iii) history of diabetes mellitus type 1 or 2 and/or treatment with antidiabetic tablets or insulin before AMI or diagnosis of diabetes mellitus based on HbA1c during AMI hospitalization, (iv) known hypercholesterolemia (total cholesterol > 200 mg/dl / LDLc > 150 mg/dl) or treatment with statins or PCSK9is, before AMI. SMuRF-less patients (Group A) are defined as those suffering an AMI in the absence of these comorbidities.

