### Statistical analysis

Clinical parametersc laboratory findings and imaging indices of interest will be compared among patients with and without SMuRFs to phenotypically characterize the SMuRF-less group, and identify any particular associations of these biomarkers with the SMuRF-less status. Subsequently, univariate logistic regression analysis will be performed to identify independent predictors of SMuRF-less AMIs. A multivariate logistic regression model will be constructed by forcing univariably significant and clinically relevant variables into the multivariable model. The G*Power software was utilized by a specialist statistician in order to calculate the sample size required to derive statistical significance. It was estimated that to detect an odds ratio > 2 with a prevalence of 15% of SMuRF-less status among AMIs, approximately 75 SMuRF-less patients will be required (with a probability for Type I error: 0.80, and statistical significance level: 0.05). Therefore, 500 patients (with and without SMuRFs) will be included in the present study. An odds ratio > 2 will be interpreted as a prediction of a 2-fold higher probability of having SMuRF-less AMI than an AMI attributed to SMuRFs.

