Baseline patient characteristics of each group will be examined and compared using the chi-square test for categorical variables and the 2-sided Student’s t-test for continuous variables or non-parametric tests (Wilcoxon, Mann-Whitney U etc.), when assumptions of normality are not met. Categorical variables will be represented by frequencies and percentages (%) and continuous variables will be summarized by mean ± standard deviation (SD) or median (1st -3rd quartile), as appropriate. In terms of statistical tests recruited for outcomes calculation, the two groups of patients will be compared to each other to identify clinical, laboratory and imaging biomarkers associated with a higher or lower probability of developing a SMuRF-less AMI. The chi-square test will be used to compare the prevalence of clinical parameters among patients with and without SMuRFs, and the t-test and Mann-Whitney U test will be utilized to compare the mean levels of laboratory and imaging biomarkers between the two groups. As mentioned before, univariate linear and logistic regression analyses will be applied to calculate univariate odds ratios, and then multivariate regression analyses will be performed. Finally, in order to identify the optimal combination of epidemiological, clinical, laboratory and imaging biomarkers associated with SMuRF-less AMIs, supervised machine learning algorithms will be used. The resulting clinical-laboratory prediction models will be evaluated with Receiver Operating Characteristic (ROC) curves.

A time-to-event analysis will be performed to assess whether the absence of SMuRFs is associated with better or worse clinical prognosis of patients (secondary outcome). Event rates will be compared by the long-rank test. Μultivariable Cox proportional hazard models will be utilized to adjust the results for clinically relevant and univariately significant variables. The 2-tailed p value of 0.05 will be considered the significance threshold for all statistical tests. All outcomes will be reported with 95% confidence intervals. Data management and statistical analyses will be conducted using SPSS software, version 26 (IBM SPSS Statistics) and R version 3.4.4 (R Foundation for Statistical Computing, Vienna, Austria).

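### Three of the four myocardial work indices contain systolic pressure, and hypertension helps define Group B, so the unadjusted comparison can flag them as imaging predictors when only pressure differs

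*Protocol article*

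**What the plan says.** **How the indices are built.** Under Data collection and study procedures: "To estimate myocardial work indices, LV GLS and peak systolic LV pressure measurements will be integrated". The abstract calls this a non-invasive calculation. The first index is "LV global work index (LVGWI, mmHg %), representing the total work within the LV pressure-strain loops"; LVGCW and LVGWW carry the same unit. The fourth, LVGWE, is a percentage given by "LVGCW/[LVGCW + LVGWW]) × 100" per cent.

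**How the groups are built.** Under Study design and population, the first of four alternative criteria for Group B is "known history of hypertension and/or antihypertensive treatment prior to AMI". For the other group: "SMuRF-less patients (Group A) are defined as those suffering an AMI in the absence of these comorbidities".

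**How they are compared.** Under Statistical analysis: "imaging indices of interest will be compared among patients with and without SMuRFs to phenotypically characterize the SMuRF-less group". For the tests, "the t-test and Mann-Whitney U test will be utilized to compare the mean levels of laboratory and imaging biomarkers between the two groups". Univariably significant and clinically relevant variables are then forced into a multivariable logistic model, and supervised machine learning searches the imaging markers together with the others. The primary outcome includes assessing these parameters as possible independent predictors of SMuRF-less infarction. Blood pressure at echocardiography is not named as a covariate, and the pressure-dependent indices are not set apart.

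**The concern.** One input to three imaging indices is linked to a criterion that defines the groups. If hypertensive patients in Group B have higher systolic pressure when the indices are measured, LVGWI, LVGCW and LVGWW will be higher in Group B even where strain is distributed identically. The planned t-test or Mann-Whitney test cannot separate the two sources, and the selection rule passes a significant result on to the models.

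Myocardial work is named in the abstract, and the Discussion presents novel echocardiographic parameters as part of the study's innovation. A lower LVGWI in SMuRF-less patients could be read as poorer ventricular performance when it reflects only the absence of hypertension. If pressure ran the other way, a real strain difference could be hidden. Dropping candidates such as HbA1c or cholesterol does not help, because the pressure sits inside the index. Hypertension history cannot serve as the adjusting variable, because it is part of the outcome definition.

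**Working it through.** **Group sizes.** The article expects 15% SMuRF-less patients: 0.15 × 500 = 75 in Group A, leaving 425 in Group B. The test is two-sided at 0.05.

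**Which indices carry pressure.** Take work as proportional to strain S times systolic pressure P. LVGWI, LVGCW and LVGWW then each contain P. If LVGCW = P·c and LVGWW = P·w, then LVGWE = P·c / (P·c + P·w) = c / (c + w), so a common pressure factor cancels.

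**Assumptions (none is in the article).** S has mean 14.5 and CV 27.5% (SD 3.99, variance 15.90) in both groups, independent of P. P has mean 125 and SD 20 mmHg in Group A. In Group B a share h of 50% or 70% is hypertensive, with pressure higher by d.

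**Formulas.**
- Group B mean P = 125 + h·d; variance of P = 400 + h(1 − h)d².
- Var(S·P) = mean(S)²·var(P) + mean(P)²·var(S) + var(S)·var(P).
- z = 14.5·h·d / √(VarA/75 + VarB/425).
- Rejection rate = Φ(z − 1.96) + Φ(−z − 1.96).

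**One case in full: d = 10, h = 0.5.**
- Difference in mean work = 14.5 × 5 = 72.5, or 5/125 = 4.0% of the Group A mean.
- VarA = 210.25 × 400 + 15,625 × 15.90 + 15.90 × 400 ≈ 338,900.
- VarB (mean P 130, variance 425) = 210.25 × 425 + 16,900 × 15.90 + 15.90 × 425 ≈ 364,830.
- Standard error = √(4,519 + 858) = 73.3; z = 0.99; rejection rate 16.7%.

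**All cases (h = 0.5 to 0.7).**

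| Excess d in hypertensive patients | Group mean gap h·d | Relative difference in LVGWI | z | Rejection rate |
|---|---|---|---|---|
| 5 mmHg | 2.5-3.5 mmHg | 2.0-2.8% | 0.50-0.69 | 7.9-10.7% |
| 10 mmHg | 5-7 mmHg | 4.0-5.6% | 0.99-1.38 | 16.7-28.2% |
| 15 mmHg | 7.5-10.5 mmHg | 6.0-8.4% | 1.48-2.06 | 31.5-54.1% |

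Simulation with the same 50-70% share gave about 8-12%, 17-26% and 34-53%, within 3 points of the closed form, and about 5% at d = 0. Adjusting for the pressure brought the rate to about 3-5% when pressures differed.

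**Other indices.** A second simulation used strain 15 (SD 4), pressure SD 18 and a wasted-work fraction of 0.10 (SD 0.03), all assumed. At 10 mmHg it gave 19-31% for LVGCW and 14-20% for LVGWW. LVGWE stayed near 5% throughout.

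**If strain is not independent of pressure.** With strain assumed to fall by 0.03-0.06 points per mmHg, a 10 mmHg excess gives 8-19% for LVGWI, while GLS itself rejects in 6-12%. At 20 mmHg and the steeper slope, GLS rejects more often (20-35%) than LVGWI (15-24%).

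**The case against.** **Group membership rests on known history or treatment, not on measured pressure.** Echocardiography follows within 24 hours of admission for an infarct. Group A may include undiagnosed hypertension, and Group B includes treated patients. No section says that pressures differ at that time. This stands: the article shows that a false difference is possible, not that it will occur.

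**The effect is diluted.** A reader might infer the size by shifting every Group B patient, which gives 45-56% at 10 mmHg and 79-87% at 15. The article does not support that, because hypertension is only one of four alternative criteria. With 50-70% hypertensive, a group-wide gap of 15 mmHg needs an excess of 15/0.7 = 21 to 15/0.5 = 30 mmHg in the hypertensive patients.

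**The plan has room for pressure.** Clinically relevant variables may enter the multivariable model, and an unseen analysis plan may list covariates. This stands in part. The article does fix an unadjusted comparison of imaging markers as its primary step, however, and a covariate in the later model does not correct that step.

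**Interpretation is already guarded.** The Discussion concedes that imaging differences may be a consequence of the infarct and calls for testing in larger trials; Limitations disclaims causality. Neither covers an index that contains a variable tied to the grouping. As pure description, lower work in patients without hypertension would be a true difference.

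**Adjustment is not neutral.** Pressure after an infarct may itself reflect ventricular function, so conditioning on it can remove part of a real difference. This stands and shapes the fix.

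**Conclusion.** The concern holds in a limited form. As planned, the comparison and selection steps can present a blood-pressure difference as an imaging predictor through LVGWI, LVGCW and LVGWW. The mechanism follows from the article's own definitions; the size does not, because no pressure or strain values are given. Under the assumptions shown, the false-difference rate for LVGWI is about 8-12%, 17-26% and 34-53% at excesses of 5, 10 and 15 mmHg in hypertensive patients. It is lower if strain falls as pressure rises, and nominal if pressures are equal at echocardiography.

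Two stronger readings are not supported. GLS is not guaranteed to be a clean comparator, since it may itself vary with pressure. Nor should a work-index association be dismissed simply because it weakens after adjustment. Only these three indices are affected; eligibility, sample size and the prognosis analysis are not.

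**What to change.** In the Statistical analysis section:

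- Report by group the systolic pressure used to calculate the indices.
- Report the group difference in LVGWI, LVGCW and LVGWW both unadjusted and adjusted for that pressure, for example by linear regression on group and pressure.
- Include that pressure whenever one of these indices is a candidate in a logistic or machine-learning model.
- Show GLS and LVGWE beside them.
- Do not describe a work-index association as independent of blood pressure unless the adjusted estimate supports it.

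The cost is small: the indices cannot be calculated without the pressure, so no new measurement is needed. It adds one model term with about 75 SMuRF-less patients. The adjusted estimate may also remove part of a real difference if post-infarct pressure reflects ventricular function, which is why both estimates should be shown.

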**Fig. 1 Fig1:**
[figure not shown]
Visual Overview of the ‘‘Beyond-SMuRFs Study’’. Study processes required for the association of SMuRF-less myocardial infarctions with patients’ clinical, laboratory and imaging biomarkers (primary outcome) are depicted. (* This figure is original and, therefore, permission for publication was not needed to be obtained from a third-party)

### Statistical analysis

Clinical parametersc laboratory findings and imaging indices of interest will be compared among patients with and without SMuRFs to phenotypically characterize the SMuRF-less group, and identify any particular associations of these biomarkers with the SMuRF-less status. Subsequently, univariate logistic regression analysis will be performed to identify independent predictors of SMuRF-less AMIs. A multivariate logistic regression model will be constructed by forcing univariably significant and clinically relevant variables into the multivariable model. The G*Power software was utilized by a specialist statistician in order to calculate the sample size required to derive statistical significance. It was estimated that to detect an odds ratio > 2 with a prevalence of 15% of SMuRF-less status among AMIs, approximately 75 SMuRF-less patients will be required (with a probability for Type I error: 0.80, and statistical significance level: 0.05). Therefore, 500 patients (with and without SMuRFs) will be included in the present study. An odds ratio > 2 will be interpreted as a prediction of a 2-fold higher probability of having SMuRF-less AMI than an AMI attributed to SMuRFs.

Baseline patient characteristics of each group will be examined and compared using the chi-square test for categorical variables and the 2-sided Student’s t-test for continuous variables or non-parametric tests (Wilcoxon, Mann-Whitney U etc.), when assumptions of normality are not met. Categorical variables will be represented by frequencies and percentages (%) and continuous variables will be summarized by mean ± standard deviation (SD) or median (1st -3rd quartile), as appropriate. In terms of statistical tests recruited for outcomes calculation, the two groups of patients will be compared to each other to identify clinical, laboratory and imaging biomarkers associated with a higher or lower probability of developing a SMuRF-less AMI. The chi-square test will be used to compare the prevalence of clinical parameters among patients with and without SMuRFs, and the t-test and Mann-Whitney U test will be utilized to compare the mean levels of laboratory and imaging biomarkers between the two groups. As mentioned before, univariate linear and logistic regression analyses will be applied to calculate univariate odds ratios, and then multivariate regression analyses will be performed. Finally, in order to identify the optimal combination of epidemiological, clinical, laboratory and imaging biomarkers associated with SMuRF-less AMIs, supervised machine learning algorithms will be used. The resulting clinical-laboratory prediction models will be evaluated with Receiver Operating Characteristic (ROC) curves.

A time-to-event analysis will be performed to assess whether the absence of SMuRFs is associated with better or worse clinical prognosis of patients (secondary outcome). Event rates will be compared by the long-rank test. Μultivariable Cox proportional hazard models will be utilized to adjust the results for clinically relevant and univariately significant variables. The 2-tailed p value of 0.05 will be considered the significance threshold for all statistical tests. All outcomes will be reported with 95% confidence intervals. Data management and statistical analyses will be conducted using SPSS software, version 26 (IBM SPSS Statistics) and R version 3.4.4 (R Foundation for Statistical Computing, Vienna, Austria).

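### Univariable significance at an unadjusted 0.05 is used to find and select "forcing univariably significant and clinically relevant variables into the multivariable model", so chance associations are likely to be reported as independent predictors

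*Protocol article*

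**What the plan says.** All of this is in the protocol article, Methods, Statistical analysis, unless another place is named.

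- Purpose given to the one-variable models: "univariate logistic regression analysis will be performed to identify independent predictors of SMuRF-less AMIs".
- Entry rule: "A multivariate logistic regression model will be constructed by forcing univariably significant and clinically relevant variables into the multivariable model".
- Error level: "The 2-tailed p value of 0.05 will be considered the significance threshold for all statistical tests".
- Size: "approximately 75 SMuRF-less patients will be required", hence "500 patients (with and without SMuRFs) will be included in the present study". The basis is "to detect an odds ratio > 2 with a prevalence of 15% of SMuRF-less status among AMIs".

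The outcome paragraph at the end of Data collection and study procedures makes the group comparisons the primary outcome and then has the same parameters assessed as potential independent predictors. It uses the language of exploration. The Discussion adds that the associations found should be tested in later, larger studies. The Background, however, names a risk stratification model as the ultimate goal.

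**The concern.** Three stated rules combine badly. The first assigns to a univariable analysis a conclusion that only an adjusted analysis can support. The second lets a variable into the adjusted model because it was significant in the same 500 patients. The third applies 0.05 to each of several dozen tests without adjustment.

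The joint model then looks like a confirmation step, but it is largely a repeat of the screen. A noise variable that got through by chance has, by selection, a coefficient that is too large in these data, and adjusting for other noise variables does little to remove it. Its p-value and 95% interval take no account of the selection. Because these comparisons are the primary outcome, the headline list of predictors may contain chance findings that nothing in the report marks as such.

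**Working it through.** **1. The plan's own figure.** 75 / 0.15 = 500, which reproduces the total. For the 75, the text gives "with a probability for Type I error: 0.80, and statistical significance level: 0.05"; I read the 0.80 as power. The prevalence of the predictor is not stated. Assume 0.40 in patients with SMuRFs. An odds ratio of 2 gives odds of 2 × 0.40/0.60 = 1.333, so a prevalence of 0.571 in SMuRF-less patients. The two-proportion formula with an 85:15 split, two-sided 0.05 and 80% power needs 77 SMuRF-less patients. With 75 against 425, power is 0.79. At prevalences of 0.20, 0.30 and 0.50 the need is 96, 81 and 81. So 75 is about right for one binary predictor tested once at 0.05.

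**2. Number of candidates.** The article gives no total. From Data collection and study procedures I count:
- age and sex (standing for demographics): 2
- socioeconomic items: 6
- physical activity, body mass index, SF-36 (as one): 3
- thyroid hormone, TSH, HbA1c, admission and peak NTproBNP and HsTnT: 7
- Lp(a), ApoB, ApoA1, IL-6, suPAR: 5
- angiographic: 3
- conventional echocardiography (LVEF, mitral inflow, annular velocities, E/e', TAPSE, FAC, S', PASP): 8
- strain: 3
- myocardial work: 4

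The sum is 41. The Discussion names about 5 more (46). Counting the blood count, biochemistry and coagulation panels as one variable each gives 49. Hence roughly 40 to 50.

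**3. The screen, if every candidate is null.** Expected false hits are m × 0.05. The chance of at least one, for independent tests, is 1 − 0.95^m.
- m = 41: 41 × 0.05 = 2.05; 1 − 0.95^41 = 0.88
- m = 50: 50 × 0.05 = 2.5; 1 − 0.95^50 = 0.92

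**4. The joint model.** All-null simulation: 500 patients, 75 of them SMuRF-less, normally distributed candidates, t-test at 0.05 as a stand-in for the univariable Wald test, survivors entered together in one logistic model. Candidates are either independent or in blocks of five with correlation 0.5.

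| Candidates | Structure | Pass the screen (mean) | Still p<0.05 jointly (mean) | Studies with at least one |
|---|---|---|---|---|
| 30 | independent | 1.5 | 1.3 | 77% |
| 30 | blocks | 1.5 | 0.8 | 58% |
| 40 | blocks | 2.0 | 1.0 | 67% |
| 50 | blocks | 2.5 | 1.2 | 73% |
| 50 | independent | 2.5 | 2.1 | 92% |

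Repeated runs of the last row gave 90% to 93%. The screen's own 92.3% (step 3) is the ceiling, so I use 92%. With 50 candidates, the joint model keeps about 85% of the screened-in noise variables if they are independent and about 49% if they come in correlated blocks.

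**5. Whether a blanket correction would do.** Bonferroni over 50 tests uses 0.05/50 = 0.001. With 75 against 425 patients, power for an odds ratio of 2 falls from 0.71–0.79 to 0.26–0.31 (predictor prevalence 0.20 to 0.50). Restoring 80% would take 168 to 203 SMuRF-less patients, or about 1,120 to 1,353 in total. That is why the fix below uses false discovery rate control.

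**The case against.** The strongest reply is that the study says it is exploratory, that a later sentence in the same section gives the right order (univariable odds ratios, then multivariable regression), and that an analysis plan not shown here may hold the candidate list, a limit on model size and a multiplicity rule. Much of this stands. The claim about independence may be a slip of wording, and the absence of a cap on model size is not a fault I can charge to an article. What remains is what the text fixes: screened variables are forced in, and 0.05 applies to all tests. Exploratory intent does not repair p-values and intervals computed after selection on the same data, and the output is still called independent predictors.

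A reader might also infer more than the document supports:
- *That univariable significance is the only gate, so that confounded factors are lost.* The entry sentence also names clinically relevant variables. On its natural reading, age or sex can enter whatever their univariable p-value.
- *That false predictors are all but guaranteed.* That is close to true only for independent candidates. Correlation is realistic here: strain feeds the myocardial work indices, and work efficiency is calculated from two of the others.
- *That the final model has 1.5 events per variable.* 75/50 = 1.5 is the ratio for candidates screened. Under the null only 2 to 2.5 enter through the screen, and the number of clinically relevant entries is not given, so overfitting of the final model cannot be shown.
- *That the protocol names 50 candidates.* It gives no number.

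**Conclusion.** The point holds in this form. The statement that univariable analysis identifies independent predictors is wrong whatever the number of candidates. The entry rule, combined with 0.05 for every test, would leave about 1.0 to 2.1 false independent predictors per study, and at least one in about 67% (40 candidates in correlated blocks) to 92% (50 independent candidates) of studies. This rests on my count of 40 to 50, on all candidates being null, and on entry through the screen alone.

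Not every candidate is null. Study design and population defines the groups partly by HbA1c-diagnosed diabetes, cholesterol and prior drug treatment. HbA1c, lipids and prior medication therefore differ between groups by construction. Significance for these says nothing about prediction, and they should not be reported as predictors.

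**What to change.** 1. Delete the statement that univariable regression identifies independent predictors. Describe those models as unadjusted associations.
2. Choose the covariates of the multivariable model in advance on clinical grounds, in a number that about 75 SMuRF-less patients can support, and drop univariable p<0.05 as a route of entry. Which variables these are is for the investigators. Prescribing a particular biomarker set would demote the clinical and imaging comparisons that the article makes primary.
3. Report the remaining comparisons one by one, adjusted for age and sex, with Benjamini-Hochberg false discovery rate control and an exploratory label, in place of 0.05 for every test.
4. Keep variables that help define SMuRF status, such as HbA1c, lipids and prior medication, out of the list of predictors; describe them only.

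No new data are needed. The cost is a change to the analysis text and an early decision on covariates. Fewer variables will be called significant, and weak associations will lose that status.
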